Further evidence of the role that functional brain networks may play in modulating response to tDCS is available from other clinical populations. For example, in people with fibromyalgia, connectivity among the thalamus, posterior insula, motor cortex and sensory cortex was a marker of better analgesic response following tDCS applied to M1 [22]. Similarly, responses to tDCS applied to the dorsolateral prefrontal cortex in people in a minimally conscious state were associated with connectivity between the dorsolateral prefrontal cortex and inferior frontal gyrus [23]. It may be that the connectivity of the network targeted by tDCS can be a useful predictor of responsiveness to brain stimulation therapy. Indeed, this may be even more critical following a stroke, where damage as a result of the lesion can interrupt functional connectivity [24].

The primary objective of this study is to determine whether connectivity of the cortical target for tDCS modulates responses to this intervention in people with stroke. The secondary objectives of this study are to determine whether facilitatory tDCS applied to the ipsilesional hemisphere in combination with an upper limb exercise program provides greater behavioral improvement compared with sham stimulation and to determine whether additional neurophysiological characteristics, such as lesion size, cortical excitability, and white matter integrity, modulate the responsiveness to tDCS. We hypothesize that the response to anodal tDCS will be variable; participants who have greater functional connectivity of the ipsilesional motor network will have stronger responses to the stimulation as shown by a greater increase in upper limb function following the intervention period. Outcomes from this study will have important implications for the clinical translation of tDCS in stroke rehabilitation. The ability to select people who will respond to this therapy could substantially improve the clinical translation of this treatment approach.

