Inclusion criteriaAged ≥18 years of ageAt least 6 months after the first ever stroke with motor impairmentMeasurable impairment of the upper limb (Fugl-Meyer upper extremity of <62 out of 66)Supportive family, friends, or carers willing to actively assist and motivate across the 2-week interventionActive wrist extension of, at least, 5°Active index finger flexion of, at least, 10°Modified Ashworth scores of <4 for the affected elbow, wrist, and metacarpal phalangeal joints

Exclusion criteriaTranscranial magnetic stimulation and transcranial direct current stimulation safety exclusion criteria as per international guidelines [25]Contraindications for magnetic resonance imagingSelf-reported neglect, apraxia, or shoulder pain (>4 out of 10 on pain visual analog scale) that would affect the ability to undertake a 1-hour upper limb exercise program.Language or cognitive impairment that would limit the ability to communicate with the research team by videoconferenceParticipation in a concurrent research study or clinical program for upper limb rehabilitation.

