### Intervention

#### Graded Repetitive Arm Supplementary Program

All participants will be provided with a home exercise program using the GRASP [26]. The GRASP protocol consists of a booklet with detailed descriptions of multiple exercises for strength, range of motion, fine motor, and goal-directed activities targeting the upper limb. The provided kit includes all required equipment to perform the exercise program. The GRASP protocol is a self-administered program with program levels (grades 1-3) individualized by a qualified occupational therapist, based on the level of impairment of the upper limb. The upper limb exercises will be performed for 1 hour per day over a 2-week period (14 sessions).

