Independent variablesFunctional connectivityTask functional magnetic resonance imagingResting state functional magnetic resonance imagingElectroencephalographyStructural connectivityFractional anisotropy index of the corticospinal tract obtained from diffusion tensor imagingAnatomicalLesion volumeDemographics and clinical characteristicsAgeGenderTime since strokeAffected hemisphere based on hand dominance

Outcome assessors will be blind to group allocation and have completed training for FM-UE and ARAT assessments through the University of California Irvine. Training outcome assessors with this approach has been shown to improve accuracy and reduce variance of the FM-UE and ARAT [33,34].

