### Statistical Analysis

Normality of data will be confirmed using Shapiro-Wilk normality tests. Where required, data will be normalized using transformations or nonparametric statistics applied. Participants’ demographics and clinical characteristics will be compared between active and sham groups. The effect of the intervention on behavioral and neurophysiological outcome measures will be investigated with a 2 Group (active, sham) × 4 Time Point (Baseline, Postintervention, 1-Month Follow-up, 3-Month Follow-up) repeated measures analysis of variance. Independent variables (Textbox 5) will be correlated with the primary outcome measure for response to anodal tDCS (change in upper limb impairment measured with the UE-FM). Where appropriate, regression models will be generated using those independent variables significantly correlated with change in upper limb impairment to identify a combination of measures associated with response to anodal tDCS. Any regression models generated will be compared using the Bayesian information criteria [45]. Where appropriate, the predictive capacity of the generated model will be investigated using a leave-one-out cross-validation. This cross-validation will be performed on participants allocated to both active and sham treatment groups to demonstrate that the predictive model is specific to the stimulation group. Statistical testing will be performed using SPSS (IBM Co, version 24.0) and significance level will be *P* ≤.05.

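### The association between connectivity and FM-UE change is open to confounding by initial severity, because baseline FM-UE has no stated role in the analysis

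*Protocol article*

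**What the plan says.** The Statistical Analysis section of the protocol article states the predictor analysis directly: "Independent variables (Textbox 5) will be correlated with the primary outcome measure for response to anodal tDCS". The response is the measure "for response to anodal tDCS (change in upper limb impairment measured with the UE-FM", that is, change in FM-UE, and no adjustment is named. The next step is also a stated rule: "regression models will be generated using those independent variables significantly correlated with change in upper limb impairment".

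Textbox 5 lists functional connectivity (task fMRI, resting-state fMRI, EEG), corticospinal tract fractional anisotropy (FA), lesion volume, age, gender, time since stroke and affected hemisphere. Baseline FM-UE is not listed, so under the stated rule it has no way into a model.

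Three other statements bear on the point:
- Textbox 1 admits participants with "Fugl-Meyer upper extremity of <62 out of 66", so baseline can be as high as 61.
- The grade of the exercise program is "individualized by a qualified occupational therapist, based on the level of impairment of the upper limb".
- For the leave-one-out step, "This cross-validation will be performed on participants allocated to both active and sham treatment groups". The stated purpose is to show that the model is specific to stimulation.

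**The concern.** Change is post-treatment FM-UE minus baseline FM-UE, so it can depend on baseline for reasons unrelated to stimulation. Participants with more or less impairment may differ in how much they gain, their exercise content differs by design, and measurement error in baseline enters change with a negative sign. Connectivity may also depend on severity: the Introduction itself says that lesion damage can disrupt functional connectivity.

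If severity is related to both, the unadjusted correlation mixes two things: whether connectivity modulates response, and whether connectivity marks how impaired the person was at entry. The first is the primary objective. A candidate biomarker could be reported that only restates baseline severity, or a real one could be missed.

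**Working it through.** The article gives no figure for this point, so the size has to be worked out under stated assumptions.

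**Inputs from the article.** Planned active group 45 and sham group 23; dropout allowance 30%; significance level .05; pilot r=0.56; power 95%. Completers are then 45 × 0.70 = 31.5, taken as 31, and 23 × 0.70 = 16.1, taken as 16.

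**Assumed inputs.** Let a be the correlation of connectivity with baseline FM-UE, and b the correlation of baseline FM-UE with change. Each is taken as 0.3 to 0.5 in absolute value.

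**Step 1: spurious correlation.** If connectivity has no effect of its own, r = a × b.
- 0.3 × 0.3 = 0.09
- 0.5 × 0.5 = 0.25

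The sign is negative if a and b have opposite signs, and positive if they have the same sign.

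**Step 2: chance of a significant result (Fisher z).** With m = atanh(|r|) × √(n − 3), two-sided rejection is Φ(m − 1.96) + Φ(−m − 1.96).

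| n | abs. r = 0.09 | abs. r = 0.25 |
|---|---|---|
| 31 | 7.7% | 27.2% |
| 45 | 9.0% | 38.0% |

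**Step 3: direction.** The hypothesis is that greater connectivity goes with greater gain. With opposite signs, at n=31 and r = −0.09, m = 0.0902 × √28 = 0.48, so a falsely supportive result has probability Φ(−0.48 − 1.96) = 0.7%. That is below the nominal 2.5%, and it shrinks further as |r| grows. Nearly all rejections then point the wrong way, and a true positive association is pulled towards zero. With same signs, nearly all rejections support the hypothesis.

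**Step 4: the ceiling on its own.** A participant entering at 61 can gain at most 66 − 61 = 5 points. A simulation took true baseline between 20 and 61 (normal, mean 40 or 50, SD 12, truncated), true gain with mean 5 and SD 4 independent of connectivity, measurement SD 2, scores capped at 66, and connectivity correlated with baseline at 0 to 0.7. All of these are assumptions.
- Correlation of baseline with change: about −0.10 to −0.14.
- Spurious correlation of connectivity with change: at most about −0.03 in size.
- Unadjusted rejection: about 4% to 6%.
- Rejection after adjusting for the error-prone baseline: about 5% to 9%.

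**Step 5: the sham check.** Power to detect a spurious r of 0.25, with atanh(0.25) = 0.2554:
- n=23: m = 0.2554 × √20 = 1.14, power about 21%.
- n=16: m = 0.2554 × √13 = 0.92, power about 15%.

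**Step 6: cost of adjusting.** For r=0.56, two-sided .05 and 95% power, N = ((1.96 + 1.645) / atanh(0.56))² + 3 = 35.45, so 36. One covariate adds 1, giving 36.45, so 37. Power for a partial correlation of 0.56 is about 91% at n=31 and 98% at n=45. The article states 47 for the unadjusted calculation, which this formula does not reproduce; that is a separate matter and does not affect this point.

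**The case against.** The strongest reply has four parts.

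*Confounding is not demonstrated.* This stands. The article gives neither correlation that would be needed, so it shows only that the analysis leaves the door open.

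*The sham group already guards against this.* A severity effect common to both arms should appear in sham as well, and the article gives the sham group this role. This stands in part. With 15% to 21% power for a spurious r of 0.25, a null result in sham would say little, and no test of a connectivity-by-group interaction is stated.

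*FA and lesion volume stand in for severity.* They are candidates, but they enter a model only if individually significant, so they do not adjust reliably.

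*Adjustment is not a clean cure.* This stands. Baseline is measured with error, and in the ceiling simulation the adjusted analysis rejected up to about 9% of the time. Some residual bias may remain.

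A reader might also infer a heavy loss of power. With a = 0.4, b = −0.4 and a baseline-adjusted r of 0.56, the unadjusted r would be 0.56 × 0.84 − 0.16 = 0.31, and power at n=31 would fall from 91% to 40%. The article does not support this. It reports 0.56 with no mention of adjustment, and for change in cortical excitability rather than FM-UE. If 0.56 is the unadjusted value, power at n=31 is about 92%. With same signs the formula gives 0.56 × 0.84 + 0.16 = 0.63, and atanh(0.63) × √28 − 1.96 = 1.96, a power of about 97.5%.

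**Conclusion.** The point holds as a gap in a stated analysis rule, not as a demonstrated bias. The predictor list and the selection rule together leave out baseline FM-UE, so the primary association is open to confounding by initial severity. The inflation in steps 1 and 2 is conditional: it rests on the assumed 0.3 to 0.5 for both correlations and on no effect of connectivity itself. The direction depends on signs that the article does not give, so masking a true association and creating false support are alternatives that cannot both occur under one sign pattern.

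A reader might blame the scale ceiling. Under the assumptions tried, the cap and measurement error alone left rejection near nominal. The risk comes mainly from a genuine link of severity with both connectivity and gain.

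One separate and minor mismatch: the Introduction sets a secondary objective on whether "additional neurophysiological characteristics, such as lesion size, cortical excitability, and white matter integrity, modulate the responsiveness to tDCS", yet Textbox 5 has no baseline corticospinal excitability. The Outcome Measures section ties Textboxes 4 and 5 to the primary question, so this is untidy rather than part of the confounding issue.

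**What to change.** In every predictor analysis, model post-intervention FM-UE with baseline FM-UE as a prespecified covariate, and keep it in all regression models whether or not it is significant. Reporting a baseline-adjusted partial correlation is equivalent: once baseline is in the model, the test of connectivity is the same whether the outcome is post-treatment score or change.

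State as a limitation that some bias may remain because baseline is measured with error, and describe the sham cross-validation as supportive rather than as proof of specificity.

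The cost is a change of wording and one degree of freedom. Baseline FM-UE is already collected, and the required N on the article's own effect size rises from 36 to 37, within the planned 45 active participants. If the adjusted effect is smaller than 0.56, power will be lower than shown here.

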#### Magnetic Resonance Imaging

MRI will be performed at the Clinical Research and Imaging Centre located at the South Australian Health and Medical Research Institute with a Siemens 3T MAGNETOM Skyra scanner (Siemens, Erlangen, Germany). Standard MRI safety screening will be performed to ensure included participants are safe for MRI. At the preintervention MRI session, the imaging protocol will have a duration of 45 minutes and include T1 MPRAGE and T2-weighted fluid-attenuated inversion recovery images, diffusion tensor imaging, resting state, and task functional MRI (fMRI). At the postintervention MRI session, the imaging protocol will have a duration of 30 minutes and include T1-weighted images, resting state fMRI, and task fMRI.

The imaging protocols are as follows: T1-weighted images (MPRAGE, voxel 1 mm × 1 mm × 1 mm, repetition time (TR)=2300 ms, echo time (TE)=2.98 ms, flip angle=9°), T2-weighted fluid-attenuated inversion recovery images (voxel 1 mm × 1 mm × 1 mm, TR=5000 ms, TE=393 ms), diffusion MRI (voxel 2 mm × 2 mm × 2 mm, TR=4200 ms, b-value=0 and 2000 s mm), resting state fMRI (voxel 2.4 mm × 2.4 mm × 2.4 mm, TR=735 ms, TE=36 ms, 2 repeats of 6-min duration, 490 measurements for each), and task fMRI (voxel 2 mm × 2 mm × 2.5 mm, TR=3000 ms, TE=30 ms, 4.44-min duration). During the task fMRI, participants will be presented with a visual cue to squeeze a stress ball in their paretic or nonparetic hand, with blocks alternating every 30 seconds and repeated 4 times per hand.

Preprocessing and statistical analyses of MRI data will be carried out using tools from the FMRIB Software Library [42]. For all voxel-wise analyses, images from participants with lesions of the right hemisphere will be flipped about the midline after registration to standard space so that all lesions appear in the left hemisphere. fMRI data will be preprocessed and analyzed using the FMRIB Expert Analysis Tool [43]. Preprocessing steps will include high-pass temporal filtering at 0.01 Hz, spatial smoothing, motion correction, and removal of nonbrain tissue. Task fMRI data will be analyzed with a boxcar regressor, which will model task and rest blocks for first-level statistical maps for each participant. Higher level mixed-effects analysis will then be run using FMRIB Local Analysis of Mixed Effects [43] to test correlations with improvement in clinical scores and compare activation maps across groups.

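### Predictors and model are chosen before the leave-one-out step, so the cross-validated predictive capacity is optimistic whenever a model is built, and the sham comparison can suggest specificity that is not there

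*Protocol article*

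**What the plan says.** The Statistical Analysis section of the protocol article sets out a sequence:

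1. **Screen.** "Independent variables (Textbox 5) will be correlated with the primary outcome measure for response to anodal tDCS", namely the change in FM-UE. The level is given as "significance level will be *P* ≤.05", and no adjustment for the number of variables screened is stated.
2. **Build.** "regression models will be generated using those independent variables significantly correlated with change in upper limb impairment".
3. **Choose.** "Any regression models generated will be compared using the Bayesian information criteria".
4. **Validate.** Where appropriate, "the predictive capacity of the generated model will be investigated using a leave-one-out cross-validation".
5. **Claim specificity.** "This cross-validation will be performed on participants allocated to both active and sham treatment groups". The stated purpose is to show that the model's predictions hold only for those who were stimulated.

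The section does not say that steps 1 to 3 are repeated when a participant is left out. It also names no test of whether a predictor's association with outcome differs between the arms.

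**The concern.** Leave-one-out cross-validation estimates performance in new people only if the left-out person played no part in building the model. Here everyone screened contributes to the choice of predictors and to the BIC comparison. Only the coefficients are re-estimated in each fold, so the choice of variables is never tested.

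The comparison with sham has a related weakness. On the likely reading, the predictors are those that happened to correlate with outcome in the active arm. Sham played no part in that choice and is half the size, so the same predictors tend to look worse there whether or not stimulation matters.

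The stated aim is a marker for choosing whom to stimulate. An inflated predictive capacity with apparent specificity would support that use on evidence that the procedure can produce by itself.

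**Working it through.** **Inputs**

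- *Arm sizes (Sample Size).* 68 split 2:1 gives 68 × 2/3 = 45.3 and 68/3 = 22.7, matching the stated 45 and 23. With the planned 30% dropout, 45 × 0.7 = 31.5 and 23 × 0.7 = 16.1. The range used is 31-45 active and 16-23 sham.
- *Candidates (Textbox 5).* One per line gives 9. Counting separate connections, EEG has 3 (ipsilesional M1 with premotor, parietal and contralesional M1) × 2 bands = 6, resting-state fMRI has 5, and the other lines give 7, so 6 + 5 + 7 = 18. The count is an assumption, so both ends are shown.
- *Screening level.* P ≤ .05, taken as two-sided.

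The plan gives no expected cross-validated figure to reproduce.

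**Step 1. Chance that a model is built when nothing predicts.** With K independent candidates this is 1 − 0.95^K:

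- K = 9: 1 − 0.630 = 37%
- K = 18: 1 − 0.397 = 60%

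**Step 2. Why leave-one-out then looks favourable.** Take one selected predictor with average leverage 2/n. Then

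R²(LOO) ≈ 1 − (1 − r²) × [(n − 1)/(n − 2)]²

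At n = 45 the smallest r that passes the screen is 0.294, so r² = 0.0864 and R²(LOO) ≈ 1 − 0.9136 × (44/43)² = +0.04. At n = 32 it is r = 0.349, r² = 0.122, and R²(LOO) ≈ 1 − 0.878 × (31/30)² = +0.06. A noise variable that only just passes the screen therefore already gives a positive cross-validated R². The validation step can hardly fail.

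**Step 3. The whole sequence, simulated.** No predictor is related to outcome, with 1,500 trials per setting. Each trial screens in the active arm, takes the BIC-best subset, and runs leave-one-out on that fixed model in both arms. R² is 1 − Σ(y − prediction)² / Σ(y − leave-one-out mean)². The nested version repeats screen and BIC in every fold.

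| Candidates | Active/sham | Model built | R² > 0, if built | Median R², if built | Median nested R², same trials | Active significant, sham not (all trials) | Nested significant in active (all trials) |
|---|---|---|---|---|---|---|---|
| 9 | 45/23 | 38.4% | 100% | 0.076 | −0.060 | 9.5% | 4.3% |
| 18 | 45/23 | 59.8% | 100% | 0.089 | −0.092 | 19.8% | 6.5% |
| 18, correlated 0.3 | 45/23 | 49.5% | 99.6% | 0.081 | −0.067 | 14.2% | 6.7% |
| 9 | 32/16 | 37.9% | 99.8% | 0.114 | −0.054 | 9.7% | 4.9% |
| 18 | 32/16 | 60.5% | 99.6% | 0.130 | −0.101 | 22.7% | 6.6% |

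Further runs over the same range give a mean R² of about +0.1 to +0.16 when a model is built, against about −0.04 to −0.12 nested.

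**Step 4. The sham arm.** Refitting the chosen variables in sham gives a median leave-one-out correlation of −0.31 to −0.40, significant in 0.7-1.5% of trials with a model. Applying the active-arm model unchanged to sham is significant in 1.6-2.7%. Nearly every false result in the active arm therefore also looks specific.

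Size works the same way. If a predictor truly had the r = 0.56 of the Sample Size section in both arms, Fisher's z gives, at n = 16, 0.633 × √13 − 1.96 = 0.32, or about 63% power. At n = 23, 0.633 × √20 − 1.96 = 0.87, or about 81%. An equally good predictor would often be missed in sham.

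**Step 5. A single pre-specified predictor.** With one candidate (45/23), a model is built in 4.8% of null trials and leave-one-out is significant in 0.3%. The problem comes from screening many variables.

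**The case against.** Several points on the other side stand:

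- **The artefact is not certain.** A reader might infer that predictive capacity and specificity will appear even if nothing works. The figures do not support that: no model is built in about 39-64% of null trials, and false specificity arises in about 9-23%.
- **Eighteen candidates and full dropout are the high end.** The 30% allowance is partly for the longer follow-up, and the time point of the FM-UE change is not fixed, so numbers after treatment may be nearer 45 and 23.
- **A real predictor is not erased.** With one true predictor at r = 0.56 and 17 noise variables, mean leave-one-out R² is 0.33 against 0.20 nested at n = 31, and 0.32 against 0.23 at n = 45. That is optimism, not a change of sign.
- **Screening in the active arm alone is inferred** from the reference to response to anodal tDCS. If the arms were pooled, the optimism would remain but the sham contrast would behave differently. Nor does the text say whether the model is refitted in sham.
- **Task fMRI.** The Magnetic Resonance Imaging section plans a group analysis "to test correlations with improvement in clinical scores and compare activation maps across groups". A reader might infer that voxels chosen on outcome feed the regression. Nothing says so, and the point is not pressed.
- **Both steps are conditional, and an unseen analysis plan might nest the selection.** The regression and the cross-validation are each to be done where appropriate. That does not correct the procedure when it is used, and the order printed here validates a model already generated.

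A further caution concerns the obvious remedy. A group-by-predictor interaction is not safe if the predictors were screened on the same active-arm data: it is then significant in about 23-29% of null trials in which a model is built.

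**Conclusion.** The concern holds in a conditional form. Selection sits outside the cross-validation, so the reported predictive capacity is optimistic whenever a model is built, and the active-versus-sham contrast cannot establish specificity. Under a global null a model is built in about 36-61% of trials, its leave-one-out R² is almost always positive, and about 9-23% of all null trials end with significant prediction in active and not in sham. Nested selection brings significant prediction in the active arm to about 4-7%.

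These sizes rest on 9 to 18 candidates that are independent or correlated at 0.3, 31-45 active and 16-23 sham participants, a two-sided screen, and screening in the active arm. The direction of the optimism does not depend on the exact values. The size of the false-specificity rate does.

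**What to change.** - **Nest the selection.** State that the correlation screen, the BIC choice and any other selection that uses the outcome are repeated inside every leave-one-out fold. Report the nested R² or prediction error as the predictive capacity.
- **Replace the specificity argument.** Do not use the comparison of cross-validation results between active and sham as evidence. Test a group-by-predictor interaction in all participants, for one connectivity measure named before unblinding, or for predictors selected without using the active-arm outcome contrast.
- **Do not test that interaction on predictors screened in the same active-arm data**, for the reason given above.

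The cost is a short script and a less favourable R². No new data are needed.
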